# The efficacy and safety of Jin's three-needle therapy vs. placebo acupuncture on anxiety symptoms in patients with post-stroke anxiety: A study protocol for a randomized controlled trial

**DOI:** 10.3389/fpsyt.2022.941566

**Published:** 2022-09-07

**Keywords:** post-stroke anxiety (PSA), Jin's three-needle therapy, sham acupuncture, CORT, ACTH, fMRI, randomized controlled trial, protocol

## Abstract

**Background:**

A large number of clinical RCTs have verified that Jin's three-needle therapy (JTNT) has a great contribution to promoting the function of paralyzed limbs and relieving anxiety disorders for patients with post-stroke anxiety (PSA). However, there is still a lack of sham needle control, and its placebo effect cannot be ruled out. This study firstly verifies the real effectiveness of JTNT. Besides, the changes in serum indexes on the hypothalamic-pituitary-adrenal axis (HPA axis) are observed dynamically by the Enzyme-Linked ImmunoSorbent Assay (ELISA). The activation of different brain regions by JTNT is recorded using resting functional magnetic resonance imaging (rs-fMRI). Therefore, we can provide more practical and powerful evidence-based medical evidence for clinical decisions.

**Method:**

This is a 16 week parallel, single-blind, random, controlled trial, including baseline, 4 weeks of treatment, and 12 weeks of follow-up. A total of 114 participants will be randomly divided into three groups in the proportion of 1:1:1. Participants will receive Jin's three-needle therapy in the active acupuncture group and accept sham needle treatment in the sham acupuncture group. In the waitlist control group, patients will not receive any acupuncture treatment. Outcomes cover three types of indicators, including scale indicators, serum indicators, and imaging indicators. The primary outcome is the change in the performance of anxiety symptoms, which is estimated by the 14-item Hamilton Anxiety Rating Scale (HAMA-14) and the 7-item Generalized Anxiety Disorder scale (GAD-7). Secondary outcomes are physical recovery and daily quality of life, which are evaluated by the National Institute of Health stroke scale (NIHSS) and the Modified Barthel Index Score (MBI Scale). Therefore, the assessment of the scale is carried out at baseline, 2nd, 4th, 8, 12, and 16 weeks. Adrenocorticotropin and cortisol will be quantitatively detected by ELISA at baseline and 4 weeks after treatment. In addition, regional homogeneity analysis (ReHo) will be used to record the activity of brain regions at baseline and 4 weeks after intervention.

**Discussion:**

The study aims to provide high-quality clinical evidence on the effectiveness and safety of JTNT for patients with PSA. In addition, this trial explores a possible mechanism of JTNT for patients with PSA.

**Clinical trial registration:**

Chinese Clinical Trial Registry, identifier [ChiCTR2200058992].

## Introduction

Stroke is the leading cause of permanent disability and death (1). Globally, more than 25 million people are diagnosed with stroke and 6.5 million people die from stroke each year, which aggravates the disease burden (2–4). Despite the existence of global policies and guidelines for stroke implementation, many challenges remain in establishing stroke services (5). In addition to residual physical disability, post-stroke anxiety (PSA) is one of the common neuropsychiatric comorbidities with a high incidence. The reported prevalence of PSA ranges from 20 to 25 percent (6–8). During COVID-19, PSA showed a noticeable peak, which is related significantly to social deprivation and the lack of rehabilitation (9). Compared to non-anxious patients, the patients with PSA are usually in more severe condition at presentation and sustain a long rehabilitation process, resulting in stroke recurrence and death (10–12). It suggests the importance of assessing anxiety and designing effective interventions in chronic stroke survivors. Unfortunately, existing stroke guidelines do not propose the best way to identify and guide the clinical treatment for PSA. Research on PSA is still in its early stages (13). A Cochrane review confirmed that current evidence is insufficient to guide the clinical treatment for PSA (14). Commonly used drugs such as selective serotonin reuptake inhibitors (SSRIs) have poor patient compliance due to their side effects (15). Therefore, more adjuvant therapy methods need to be developed.

Traditional Chinese medicine (TCM) has been used to treat cerebral apoplexy since 3,000 years ago and accumulated abundant and robust evidence (16). Acupuncture, as an important part of TCM, has a solid foundation in China to be applied to improve neurological impairment and complications induced by stroke (17). Jin's three-needle therapy (JTNT), established by Jin Rui, was standardized in one of the National research projects and promoted as the popular acupuncture method in Southern China (18–20). A large number of RCTs have confirmed the efficacy of JTNT in treating mental diseases such as PSA (21, 22). However, there is no placebo-controlled evidence to support it. The real efficacy of JTNT for patients with PSA remains to be proven, and its mechanism has not been fully elucidated.

It is indispensable to identify the cause and pathogenesis of PSA for targeted therapies. According to the available research results, PSA is multifactorial, involving biological and neurophysiological factors. The hypothalamic-pituitary-adrenal (HPA) axis is one of the neuroendocrine systems in the brain that controls the release of glucocorticoids from the adrenocortical glands (23). As well as being a component of the stress response, it also mediates additional downstream pathophysiological changes (24). Hypothalamic hormones stimulate corticotroph cells in the anterior pituitary to secrete adrenocorticotropin (ACTH) (25, 26). ACTH activates the synthesis and secretion of glucocorticoid cortisol (CORT) by the human adrenal cortex (27, 28). As a result of the variety of releasing factors, the HPA axis is expected to respond to stimulation quickly and dynamically. Clinical studies suggest that immediately after stroke onset, a massive release of pro-inflammatory cytokines activates the HPA axis (29, 30). The activated HPA axis promoted a “systemic anti-inflammatory response” that negatively affects function recovery and anxiety generation (31). Besides, anxiety and depression are recognized to be associated with dysregulation of the HPA axis, which accentuates inflammation, consequently increasing the risk of stroke recurrence (32). Dysfunction of the HPA axis is suspected to be one of the main mechanisms connecting stroke with anxiety (33). This study provides preliminary biological evidence for the potential efficacy effect of acupuncture on PSA.

Resting-state functional magnetic resonance imaging (rs-fMRI) is an effective and non-invasive technique to record the activity of the brain in various neuropsychiatric disorders including PSA (34–36). It is revealed that the main regions related to anxiety effects are hippocampus, thalamus, frontal lobe, amygdala, insular cortex, and prefrontal cortex (37–40). The hypothesis of our study is to explore the underlying neural mechanisms of PSA through blood-oxygen-level-dependent effects (41). Regional homogeneity (ReHo) is used to process the fMRI images (42). To evaluate resting-state brain activity effectively, Kendall's coefficient of concordance (KCC) is used to compare a given voxel's time series with its nearest neighbors (43). ReHo theory states that in an area where ReHo is increased, the connections between neurons are strengthened. Conversely, the presence of reduced ReHo indicates a weakening of local connections between neurons. ReHo has shown to be a highly sensitive and reliable method for determining the regional activity level of each voxel in the brain of a single individual (44). Yet, few studies have investigated how acupuncture modulates brain regions in patients with PSA using fMRI. As a result, we use rs-fMRI to explore the possible changes in brain activity and try to find the associations among brain activity, disease activity, and anxiety statuses. This study provides preliminary neurophysiological evidence for the potential efficacy effect of acupuncture on PSA.

In recent years, JTNT has increasingly attracted the attention of clinicians and researchers. However, there is insufficient evidence about the real effects of JTNT on PSA patients. Therefore, we hypothesize that acupuncture will have better clinical efficacy than sham acupuncture in clinical symptoms, anxiety degree, and quality of life. We try to investigate the potential mechanism by enzyme-linked immunosorbent assay (ELISA) and rs-fMRI.

## Methods and analysis

### Ethical standard and study registration

The protocol was registered with the China Clinical Trial Registry (item number: ChiCTR2200058992), and this study protocol has been approved by the Ethics Committee of the First Affiliated Hospital of Guangzhou University of TCM (item number: K2022-02).

### Informed consent

Participants will have sufficient time to decide whether to participate in this trial. Before this trial, patients will have the right to obtain all relevant information about the trial including the benefits and risks, and they will have the right to withdraw from it if needed. As part of the recruitment process, all participants will be required to provide written informed consent before the trial. All participant records will be kept confidential.

### Study design

A single-center, prospective, randomized controlled trial (RCT) will be conducted at the First Affiliated Hospital of Guangzhou University of TCM. A total of 114 participants with PSA will be recruited and randomly assigned to conventional therapy plus JTNT, conventional therapy plus sham acupuncture, or conventional therapy only. Both JTNT and sham acupuncture are provided five times per week for 4 weeks. Outcomes cover three types of indicators, including scale indicators, serum indicators, and imaging indicators. The primary outcome is the change in the performance of anxiety symptoms, which is estimated by the 14-item Hamilton Anxiety Rating Scale (HAMA-14) and the 7-item Generalized Anxiety Disorder scale (GAD-7). Secondary outcomes are the physical recovery and daily quality of life for patients with PSA, which are evaluated by the National Institute of Health Stroke Scale (NIHSS) and the Modified Barthel Index Scale (MBI). The evaluator will evaluate and analyze the results at six points (baseline, 2nd, 4th, 8, 12, and 16 weeks). ACTH and CORT will be quantitatively detected by ELISA at baseline and 4 weeks of treatment. In addition, ReHo will be used to record the brain regions activity at baseline and 4 weeks after intervention. The flow chart of the trial is illustrated in Figure 1, while Table 1 shows the schedule of measurements.

**Figure 1 F1:**
[figure not shown]
Flow diagram of the study procedure.

**Table 1 T1:** Study schedule showing the time points for enrollment and assessment.

	**Study period**							
**Timepoint**	**Enrollment (1 week)**	**Baseline**	**Treatment phase (4 weeks)**			**Follow-up phase (12weeks)**		
	**week 1**	**0 week**	**Week 2**	**Week 4**		**Week 8**	**Week 12**	**Week 16**
**Enrollment**								
Informed consent	×							
Eligibility screen	×							
Medical history	×							
Merger disease	×							
Randomization		×						
Allocation		×						
**Interventions**								
Intervention group								
Control group								
**Assessments**								
HAMA-14		×	×	×		×	×	×
GAD-7		×	×	×		×	×	×
NIHSS		×	×	×		×	×	×
MBI		×	×	×		×	×	×
CORT		×		×		×	×	×
ACTH		×		×		×	×	×
fMRI		×		×				
**Safety**								
Safety evaluation		×		×				
Adverse events								

^×^, required; HAMA, 14-item Hamilton Anxiety Scale; GAD-7, 7-item Generalized Anxiety Disorder-7 Scale; NIHSS, National Institute of Health stroke scale; MBI, the Modified Barthel Index Scale.

### Participant recruitment

Those who occur anxiety more than 1 week after a stroke are diagnosed with PSA according to guidelines customized by The American Psychiatric Association. A target sample of 114 participants will be recruited in the acupuncture outpatient and inpatient systems at the First Affiliated Hospital of Guangzhou University of TCM. The trial will start in May 2022 and run until December 2024. To recruit potential patients, recruitment advertisements will be posted on WeChat, acupuncture outpatient, inpatient systems, and other official platforms. Brief introductions about inclusion criteria, possible benefits for patients, and contact information for the researcher will be provided in the advertisements.

### Inclusion criteria

Participants with the following conditions are included:

(1) The age is between 30 and 75, and gender is not limited.(2) Diagnosed with stroke (cerebral infarction) within 2 weeks to 3 months and patients who have not had a previous stroke.(3) Met the diagnostic criteria for “Anxiety disorder due to another medical condition” in the Diagnostic and Statistical Manual of Mental Disorders, Fifth Edition (DSM-V) (45).(4) The HAMA score ≥14 points, and <29 points.(5) Clear consciousness, stable vital signs, no cognitive impairment, and ability to cooperate with the scale assessment.(6) Have not taken anti-anxiety drugs systematically.(7) An informed consent is signed by patients or their immediate family members.

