### Randomization

The randomization sequence will be generated by an independent statistician, who will not participate in other procedures of the trial, using the SAS 9.3 statistical analysis system (SAS Institute Inc., Cary, NC, USA). To guarantee allocation concealment, the generated list of random numbers will be placed into sequentially numbered, opaque, sealed envelopes. A special information manager will be designated to keep information secure. Researchers need to contact the designated information manager to get a random number and group information for each participant included in the study.

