### Blinding

Following the information from the envelope, each participant will be randomly assigned in a 1:1:1 ratio to active acupuncture group, the sham acupuncture group or the waitlist group. Acupuncturists, who had received the prepared standard operating procedure guidance for 2 weeks, will be appointed to perform the acupuncture treatment for both groups separately. The blinding acupuncture device has obtained the national utility model patent certificate (patent number: ZL 202121352221.7). It is a validated device that consists of one tube, one needle base with multiple angle openings, one open or sealing adhesive base, and a pointy or flat acupuncture needle. Figure 2 details the blinding device. The customized blinding needles are produced by a manufacturer with relevant qualifications (Guangzhou Suixin Medical Equipment Co., Ltd.). Before our research, patients will be informed that they may have either “less painful acupuncture” (sham needles) or “traditional Chinese acupuncture” (real needles). As the sham acupuncture in this study can create similar pain to acupuncture without penetrating the skin, it can serve as an effective blinding tool. To maximize blinding effect, both groups will be given identical blindfolds during the treatment. Even so, it is impractical to blind the acupuncture operators due to the acupuncture procedure. In an attempt to minimize the subjective influence, statisticians and data managers, as independent three-party to the research, will also be blinded to the group information.

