### Sample size

The sample size was calculated by the primary outcome. According to the results of preliminary pre-experiment, the Mean ± SD of HAMA score in patients who received conventional therapy plus JTNT was 14.25 ± 7.10, while it was 19.46 ± 4.80 in patients who received conventional therapy plus sham acupuncture. Statistical power is set at 0.90, alpha is set at 0.05, and two-sided tests are performed. After calculations performed by PASS 15.0 (NCSS LLC. Kaysville, Utah, USA) software, 30 people are estimated for each group. The estimated loss to follow-up rate is 20%, so each group will eventually need to include 38 people. The formula for sample size calculation is as follow. Therefore, to verify the placebo effect of sham acupuncture, a waiting group was recruited. The number of participants in the waitlist control group is equal as the sham acupuncture group. Finally, a total of 114 participants will be randomly divided into three groups in the proportion of 1:1:1.

(1)
$$\begin{array}{l} N=\frac{{\left(Z_{\alpha }+Z_{\beta }\right)}^{2}*2\sigma^{2}}{\delta^{2}} \end{array}$$

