### The secondly outcome

The secondary outcomes are the physical recovery and daily quality of life for patients with PSA, which are evaluated by the National Institute of Health stroke scale (NIHSS) and the Modified Barthel Index Scale (MBI). Besides, secondary outcomes will be obtained using ELISA and fMRI scanning. ELISA will be used for quantitative analysis of the content of CORT and ACTH in serum.

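### The stated between-group tests leave out time since stroke despite an entry window of 2 weeks to 3 months: precision is lost and a marked chance imbalance would go uncorrected, but the trial is not biased

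*Protocol article*

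**What the plan says.** Inclusion criterion (2) of the protocol article reads "Diagnosed with stroke (cerebral infarction) within 2 weeks to 3 months and patients who have not had a previous stroke". The interval from stroke must therefore be known for every patient before entry.

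The Introduction states that "immediately after stroke onset, a massive release of pro-inflammatory cytokines activates the HPA axis", and adds that the activated axis has an adverse effect on recovery of function and on the generation of anxiety. Under the secondary outcomes, "The secondary outcomes are the physical recovery and daily quality of life for patients with PSA", measured by NIHSS and MBI; serum ACTH and CORT and fMRI are secondary as well.

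On allocation, "The randomization sequence will be generated by an independent statistician, who will not participate in other procedures of the trial", "the generated list of random numbers will be placed into sequentially numbered, opaque, sealed envelopes", and "each participant will be randomly assigned in a 1:1:1 ratio to active acupuncture group, the sham acupuncture group or the waitlist group". Strata, blocks and minimisation are neither mentioned nor ruled out.

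Under Clinical data analysis, groups are compared by independent t-test, or by a rank test where normality or equal variance fails. No covariate enters these comparisons. Under MRI data analysis, ReHo is also compared between groups by independent t-tests. Age and education appear there as examples of covariates, but only for the correlation of scale improvement with brain regions.

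**The concern.** One patient may enter at about 14 days after infarction and another at about 91 days. The protocol gives its own reason to expect that a process set off by the stroke bears on the outcomes it measures, and it intends to read before-and-after change in ACTH and CORT as evidence on the mechanism of JTNT. If change in NIHSS, MBI or hormones depends on when a patient enters, an unadjusted comparison has two costs:

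- Variation that could be explained stays in the error term, so intervals are wider than they need be.
- If the arms happen to differ noticeably in time since stroke, the stated analysis has no means of separating that difference from a treatment effect.

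The authors consider covariates for one imaging analysis but not for the between-group comparisons, although this one is already known at screening.

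**Working it through.** **Step 1. The planned size.** Inputs from the Sample size section: "the Mean ± SD of HAMA score in patients who received conventional therapy plus JTNT was 14.25 ± 7.10" and "19.46 ± 4.80 in patients who received conventional therapy plus sham acupuncture", power 0.90, two-sided alpha 0.05.

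- Difference: 19.46 − 14.25 = 5.21.
- Pooled SD: √((7.10² + 4.80²)/2) = √36.725 = 6.06.
- n = (1.96 + 1.2816)² × 2 × 36.725 / 5.21² = 28.4, so 29 by the normal formula. Power based on the t distribution is 0.894 at 29 and 0.904 at 30, so 30.
- 30/(1 − 0.20) = 37.5, so 38 per arm; 3 × 38 = 114.

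The stated figures reproduce, and the present point does not depend on them beyond the 38 per arm.

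**Step 2. How far the arms can differ by chance.** Assumptions, not in the article: entry time uniform from 14 to 91 days, and no balancing on it.

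- SD = 77/√12 = 22.2 days.
- SE of the difference in means = 22.2 × √(2/38) = 5.1 days.
- 95% range = ±1.96 × 5.1 = ±10.0 days, or ±0.45 SD.
- Probability of a difference above 0.25 SD: 28%; above 0.5 SD: 3%.

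**Step 3. False positives.** 20,000 simulated two-arm trials with no treatment effect and 38 per arm, for each assumed correlation ρ between time since stroke and outcome change:

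| ρ (R² = ρ²) | Unadjusted t-test, all trials | Unadjusted, imbalance > 0.4 SD (about 8% of trials) | ANCOVA, same 8% | Reduction in SE from ANCOVA |
|---|---|---|---|---|
| 0 (0%) | 5.1% | 5.2% | 5.2% | none |
| 0.3 (9%) | 4.8% | 8.7% | 5.1% | 4% |
| 0.5 (25%) | 4.8% | 14.4% | 4.6% | 13% |
| 0.7 (49%) | 4.9% | 27.9% | 4.4% | 28% |

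Over all randomisations the error rate is nominal. It rises only after an unlucky draw (0.4 × 22.2 = 8.9 days or more), and adjustment removes that rise.

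**Step 4. Gain in precision.** With R² the share of outcome variance explained, the effective sample size grows by 1/(1 − R²).

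- R² = 0.05: 1/0.95 = 1.05. The SE is multiplied by √0.95 = 0.975, so it is 2.5% smaller.
- R² = 0.15: 1/0.85 = 1.18. The SE is multiplied by √0.85 = 0.922, so it is 7.8% smaller.

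This range corresponds to ρ of about 0.22 to 0.39. Only the 0.3 row of the table lies within it; the 0.5 and 0.7 rows show what a stronger relation would do.

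**The case against.** The best case against acting is that unstratified randomisation is valid, that chance imbalance is already allowed for in the 5% error rate, and that the same could be said of any prognostic factor in any trial. The first two parts stand, and Step 3 confirms them. The third is weaker here, because the article itself supplies a reason why timing after stroke could matter.

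Other objections that stand in part:

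- **No time course is given.** The Introduction describes activation at onset only, and the first two weeks are already excluded. A reader might infer that the protocol concedes HPA settling and spontaneous recovery across the entry window; it does not. For anxiety, the Discussion says incidence did not fall significantly over 24 months. The strength of the relation is therefore an assumption throughout.
- **The shift is modest.** An imbalance at the edge of the 95% range moves the arm difference by ρ × 1.96 standard errors. For ρ of 0.22 to 0.39 that is 0.4 to 0.8 of a standard error.
- **The outcomes concerned are secondary.** The primary outcome is anxiety on HAMA-14 and GAD-7.
- **The article is silent on strata.** A reader might infer that the list is unstratified and call that a defect. A condensed article commonly leaves strata and block size to the full protocol, so the silence proves nothing. Any cut-point within the window would also be a matter of preference.

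None of this answers the point about the analysis. There the article is not silent: it names unadjusted tests.

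**Conclusion.** The point holds as one of precision and robustness in the stated analysis of secondary outcomes. The wide entry window, the unadjusted between-group tests and the absence of time since stroke from every stated analysis are all on the page.

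The gain from adjusting is about 5% to 18% more patients' worth of information if R² is 5% to 15%, and close to nothing if timing turns out not to predict outcome. In the roughly 8% of randomisations with an imbalance above 0.4 SD, adjustment brings the false-positive rate from about 9% (ρ = 0.3) back to about 5%. These figures rest on the assumed uniform entry times, the assumed correlations and 38 analysed per arm.

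The stronger reading, that the design biases the trial or lets imbalance systematically pass for a JTNT effect, is not supported, because the overall error rate is unaffected.

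**What to change.** Before unblinding, replace the unadjusted between-group t-tests for NIHSS, MBI, ACTH and CORT, and the ReHo group comparison, with ANCOVA or a linear model that includes treatment arm, the baseline value of the outcome and days from stroke to randomisation. Tabulate days since stroke by arm with the other baseline data, so that any imbalance is visible.

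The cost is one degree of freedom for days since stroke and a little extra analysis work. The interval is already needed to check eligibility, so no patients, visits or assessments are added, and the change remains possible for patients already randomised. Stratifying the allocation list by time since stroke is optional and forms no part of this recommendation.
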